### Sample size determination

VICTOR uses a Bayesian approach to estimation and decision-making, based on the design proposed by Neuenschwander and colleagues [33]. The one-year mEFS rate on DAGO is expected to be 63% based on molecular monitoring and clinical outcome data from patients aged ≥ 60y with the genotype *NPM1*^mut^
*FLT3* ITD^neg^ treated with IC (Unpublished observations, [name]). A decrease of this one-year mEFS rate on VEN + LDAC to 55% would be acceptable given the benefits of VEN + LDAC in comparison to DAGO, this equates to a non-inferiority margin in terms of hazard ratios of 1.29. Further to this, there is potential for the VEN + LDAC arm to actually be superior to DAGO in terms of mEFS. Phase II data (*n* = 27) gave a 2-year overall survival rate of 75% with VEN [34], which could be extrapolated back to suggest that a 1-year mEFS rate of 75% may be a realistic outcome which equates to a superiority HR of 0.62.

As a phase II proof of concept trial that is aiming for a moderate sample size, it is recognised that a more liberal type I and type II errors are acceptable. We have selected a one-sided alpha-level of 20% that then defines our decision criteria at the final analysis. We have also specified an additional criterion for the sample size to ensure that when the observed final estimate for the mEFS HR attains a required critical value of 1.1 then statistical significance will be achieved, i.e., this is the maximum observed values that would generate a “go” decision under the Bayesian framework specified above. A critical value marginally greater than 1 was chosen because of the potential substantial patient benefits of VEN + LDAC over DAGO. Statistical simulations show that 116 events are required to achieve the criteria specified above. In addition, with this number of events, the design has an 80% probability to correctly conclude non-inferiority when the true HR is 0.94. With a 2-year recruitment period, a 2-year follow-up period and expected one-year mEFS rate of 63%, we predict that the trial needs to recruit a total of 156 patients in order to observe the 116 events required for the trial.

The sample size calculation is based on recruitment of patients aged ≥ 60 years. If non-inferiority of VEN + LDAC is demonstrated, younger patients aged 50–59 years may be recruited in a parallel cohort. It is estimated that an additional 30–50 patients will be recruited in the younger cohort to allow an evaluation against the older cohort to determine if the trend in effect is comparable. There is no formal statistically-based sample size calculations for this additional cohort and no set minimum/maximum number of patients.

The trial is adaptive and will allow a staged expansion of the population to include younger patients as evidence emerges of non-inferiority in the older patients. This decision will first be considered at the interim analysis when 50 patients have been recruited and have sufficient follow up. Further evaluation can take place at later time points if the DMC require further certainty.

### Tissue and blood samples

The blood and bone marrow sampling schedule reflects UK standard of care practice as far as possible, so that trial patients will not be exposed to a greater number of sampling procedures than those treated off-study. A bone marrow aspirate and trephine sample will be taken during screening; samples will be taken for local morphology, histopathology, cytogenetics and flow cytometry and in addition an aspirate sample will be sent to the trial laboratory. Aspirates will then be taken at the end of each cycle for cycles 1–4 (once cell counts have recovered) to determine morphological response assessment; an aspirate sample will also be sent to Guy’s Hospital at each time point for molecular response assessment. A trephine will only be required during follow up if cell counts have not recovered by day 42 of the cycle, to confirm a MLFS. Following the first four cycles of treatment, a bone marrow aspirate will be performed and at month six (which will usually be the post-cycle 4 time point), and then every three months for two years from trial entry, unless the post cycle four bone marrow aspirate tests minimal residual disease (MRD) positive with a reduction of less than 4 log_10_ from baseline and this is confirmed on a second sample. In this case molecular persistence is diagnosed and patients should change treatment, as outlined above. If the sample is MRD positive but the reduction is more than 4 log_10_ from baseline, bone marrow aspirates should be performed every 4–6 weeks until the patient enters molecular complete remission, experiences molecular failure, or the levels have been stable for > 3 months, when the frequency of monitoring may be reduced to every three months.

A peripheral blood sample will be collected at diagnosis to determine eligibility, this will be sent fresh to the trial laboratory for rapid screening for *FLT3* and *NPM1* mutations, which is performed and reported within 24 h of sample receipt. Following trial entry, paired peripheral blood samples will be taken at the same time as bone marrow aspirates i.e., baseline (an additional pre-treatment blood sample is required as a baseline sample), after each cycle of treatment for four cycles, then at month six (which will be the post cycle 4 sample for most patients), then three-monthly for two years from trial entry. These samples will be shipped fresh for patients in the UK and Denmark together with the paired bone marrow aspirate. For patients in New Zealand, both peripheral blood and bone marrow samples will be processed to cDNA in Auckland and then sent to London.

All samples will be collected in accordance with national regulations and requirements including standard operating procedures for logistics and infrastructure. Samples will be taken in appropriately licensed premises and transported in accordance with the Human Tissue Authority guidelines and NHS trust policies.

### Adverse events reporting and analysis

The collection and reporting of adverse events (AEs) as measured by National Cancer Institute (NCI) Common Terminology Criteria for Adverse Events (CTCAE), version 4.0 [35], will be in accordance with the Research Governance Framework for Health and Social Care and the requirements of the National Research Ethics Service. Definitions of different types of AEs are listed in online Supplementary Appendix 6. The reporting period for AEs will be between the date of commencement of protocol defined treatment for up to 28 days after the last dose of investigational medicinal product (IMP). The investigator should assess the seriousness and causality (relatedness) of all AEs experienced by the patient (this should be documented in the source data) with reference to the protocol. All grade 3 and above medical occurrences which meet the definition of an AE should be reported, with the exception of abnormal laboratory findings which should only be reported if the event:Results in the early discontinuation of trial treatment, and/or;Requires a dose modification or interruption or any other therapeutic intervention or is judged to be of significant clinical importance.

If a laboratory abnormality is one component of a diagnosis or syndrome, then only the diagnosis or syndrome should be recorded as an AE. Pre-existing conditions should only be reported if the condition worsens by at least one CTCAE grade. All AEs will be reported using the applicable electronic case report form (eCRF).

The following events should not be reported as serious adverse events (SAEs):

Hospitalisations for:

Protocol defined treatmentPre-planned elective procedures unless the condition worsensTreatment for progression of the patient’s cancer

Progression or death as a result of the patient’s cancer (unless the investigator considers it related to study treatment), as this information is captured elsewhere on the Case Report Form.

Development of neutropenia (< 1.0 × 10^9^/L) or thrombocytopenia (< 50 × 10^9^/L) within 42 days of the start of the treatment cycle.

Events that do not require expedited (immediate) reporting which will be reported on an expected serious adverse reaction (SAR) form.

Patients receiving chemotherapy may require admission to hospital for appropriate medical intervention following development of some of the more severe known side effects of treatment. For this reason, infection-based SAEs do not require expedited (immediate) reporting by site and are not regarded as unexpected for the purpose of this trial, unless the event proves fatal or requires admission to a high dependency or intensive care facility. An expected SAR form can be completed for these specific events instead of an SAE form.

One of the main adverse events associated with the use of VEN is tumour lysis syndrome. This syndrome occurs when an effective treatment causes a large number of cancer cells to die quickly, resulting in electrolyte and metabolic abnormalities which can cause nausea, seizures, kidney damage, cardiac toxicities and death. Tumour lysis syndrome is largely seen in chronic lymphoblastic leukaemia patients treated with VEN; with studies in AML have not demonstrated TLS to be an adverse event of concern in this population [20–22]. However, tumour lysis syndrome will be included as an adverse event of special interest during VICTOR and should be reported as a SAE.

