**Fig. 1 Fig1:**
[figure not shown]
VICTOR trial schema VICTOR trial schema showing the patient pathway highlighting treatment decisions depending on disease status. #, cycles; CR, complete remission/response; DA, daunorubicin; DAGO, daunorubicin, cytarabine and gemtuzumab ozogamicin; FLAG-IDA, fludarabine, cytarabine and idarubicin; HIDAC, high-dose cytarabine; LDAC, low-dose cytarabine; MRD, minimal residual disease; R, randomisation; VEN, venetoclax

Randomisation will be 1:1 performed electronically using a computer program developed by the Cancer Research UK Clinical Trials Unit (CRCTU), Birmingham, UK. Stratification variables are:Age (60–69 years versus 70 + years (a further variable of 50–59 years to be included when/if required))SexPerformance status (0 versus 1 and 2)

This trial aims to recruit patients at participating centres following referral for suspected AML or at multi-disciplinary team meetings allowing referral to the trial site from other centres in the UK, Denmark, and New Zealand. Recruitment will be over two years, with participants followed up for at least two years. A list of the VICTOR trial centres can be requested from the VICTOR Trial Office ([contact]). The Standard Protocol Items: Recommendations for Intervention Trials (SPIRIT) checklist is provided as Supplementary Appendix 1 [27]. The World Health Organization (WHO) Trial Registration Data Set is provided in Supplementary Appendix 2.

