### Interventions

In both arms, cycles are up to 42 days in duration; this includes a 28-day treatment cycle with days 29–42 to allow for neutrophil and platelet count recovery. Patients will be assessed for response after each cycle of treatment once counts have recovered for the first 4 cycles, and subsequently every 3 cycles from cycle 6 onwards. The permitted dose schedules for both arms are described in Table 2.

**Table 2 Tab2:** Permitted treatment schedules within the VICTOR trial

Drug	Dose	Method	Day of Cycle

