**Venetoclax and Low-dose Cytarabine Arm**			
**Cycle 1** (inpatient^α^)			
Cytarabine	20 mg/m^2^	Subcutaneous^β^	1–10
Venetoclax	100 mg	Oral	1
	200 mg	Oral	2
	400 mg	Oral	3
	100 mg	Oral	4–28
**Cycles 2–4** (outpatient (up to 12 cycles may be given))			
Cytarabine	20 mg/m^2^	Subcutaneous^β^	1–10
Venetoclax^γ^			
Either	100 mg	Oral	1–28
Or	600 mg	Oral	1–28
Accompanying supportive care (one of the following is mandated during all cycles):			
Aciclovir	400 mg twice a day	Oral	1–28
Valaciclovir	500 mg once a day	Oral	1–28
Posaconazole	300 mg twice a day	Oral	4
	300 mg once a day		5–28
Voriconazole	400 mg twice a day	Oral	4
	200 mg twice a day		5–28
Optional supportive care (one of the following is permitted):			
Ciprofloxacin	500 mg twice a day		1–28
Levofloxacin	500 mg once a day		1–28

^*^ May be administered as per local practice

^**^ If current standard of care is treatment in ambulatory care setting or outpatient day unit, this is permitted at the discretion of the treating investigator

^#^ Unless local standard practice is to dose cap at 4.5 mg

^†^ Gemtuzumab ozogamicin (GO) should be given on days 4 and 7 if white blood cell count ≥ 30 × 10^9^/L on day 1. For New Zealand sites standard of care will consistent of daunorubicin and cytarabine only until GO is available for use

^α^ Patients should generally be admitted to hospital for cycle 1 of treatment unless there are established local protocols for ambulatory management of induction therapy

^β^ Method of administration may be as per local practice, including self-administration

^γ^ 100 mg dose used if patient remains on anti-infective prophylaxis, 600 mg if patients stop anti-infective prophylaxis

Following cycle 1 the starting criteria for each cycle (cycle 2–4 of DAGO and cycle 2–12 of VEN + LDAC) are a neutrophil count > 1.0 × 10^9^/L and a platelet count > 75 × 10^9^/L. The subsequent cycle may be delayed by a further two weeks until the counts recover, however, if not recovered six weeks after the start of the preceding cycle (i.e., by day 42), a bone marrow aspirate and trephine will be performed to confirm a morphological leukaemia free state (MLFS). If confirmed, and in the absence of molecular progression, a further delay in treatment may be recommended after discussion with the clinical co-ordinators. If a MLFS is not confirmed, patients may receive salvage chemotherapy.

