The FLAG-Ida regimen is recommended for salvage therapy as detailed below and adjusted according to the patient’s age as follows (although the final decision on salvage regimen will be made by investigators, taking into account performance status and other co-morbidities).Age < 60: Fludarabine 30 mg/m^2^ (D1-5), cytarabine 2000 mg/m^2^ (D1-5) and idarubicin 8 mg/m.^2^ (D3-5)Age 60–69: Fludarabine 30 mg/m^2^ (D1-5), cytarabine 1000 mg/m^2^ (D1-5) and idarubicin 8 mg/m.^2^ (D3-5)Age ≥ 70: Fludarabine 25 mg/m^2^ (D1-5), cytarabine 1000 mg/m^2^ (D1-5) and idarubicin 5 mg/m.^2^ (D3-5)

Granulocyte-colony stimulating factor is given daily on days 1–5 and then from day 10 until neutrophil count recovery (> 1.0 × 10^9^/L) for all patients. Supportive care should be given according to local guidelines for this regimen which should include prophylaxis for *Pneumocystis pneumonia*.

In the following circumstances, the VICTOR trial allows for patients randomised to receive standard of care (DAGO) to crossover to receive VEN + LDAC treatment for up to 12 cycles:Any patient who meets criteria to receive salvage chemotherapy, but is judged by the investigator to be unfit to receive this for any reason.Any patient who has received salvage chemotherapy and meets criteria to receive a transplant but cannot receive this because of comorbidity, performance status or donor availability.Any patient who has received salvage chemotherapy but who experiences molecular progression.Any patient who has received a transplant and experiences molecular persistence, molecular progression or molecular relapse.

Patients who crossover will be followed up for all trial outcome measures; the occurrence of molecular complete remission after crossover, molecular event-free survival time and overall survival time from crossover will be reported descriptively in this single cohort of patients. The VICTOR schedule of events has been included in Supplementary Appendix 5.

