### Trial outcomes

The primary outcome is molecular event-free survival time (mEFS) where an event is defined as follows:Failure to achieve morphological CR or CR with incomplete blood count recovery (CRi) after two cycles of therapy;Molecular persistence, progression or relapse requiring treatment change;Morphological relapse, or;Death.

Morphological CR is defined as < 5% blasts in a cellular bone marrow with neutrophil count ≥ 1 × 10^9^/L and platelet count ≥ 100 × 10^9^L, and CRi as < 5% blasts but with neutropenia (neutrophil count < 1 × 10^9^/L) or thrombocytopenia (platelet count < 100 × 10^9^/L) [28].

Molecular persistence is defined as detectable *NPM1* mutant transcripts present after completion of treatment with less than a 4 log_10_ reduction from baseline in the bone marrow, confirmed on a second consecutive sample; molecular progression an increase in *NPM1* mutant transcript levels by > 1 log_10_, confirmed on a second sample, and molecular relapse as detectable *NPM1* mutant transcripts, confirmed on a second consecutive sample showing an increase of > 1 log_10_ in a patient who previously tested negative in at least one technically adequate bone marrow sample (i.e., *ABL* C_t_ < 26.5 or *ABL* copy number > 10,000) [29].

Morphological relapse is defined as ≥ 5% blasts in the blood or bone marrow in a patient with a previously documented CR, CRi or morphological leukaemia free state (MLFS: < 5% bone marrow blasts, no auer rods or extramedullary disease, does not meet criteria for CR or CRi (i.e., blood count recovery is below the specified levels) [28].

Secondary outcomes include: Occurrence of morphological complete remission (CR or CRi) by the end of the second cycle of treatment; death within 30 and 60 days from trial entry; overall survival time (OS) from date of randomisation; time to morphological relapse from date of morphological complete remission; time to molecular relapse from date of molecular complete remission; cumulative occurrence of grade 3 and 4 adverse events at 12 and 24 months; prevalence of molecular complete remission at month 3, 6 and 12; cumulative resource use at 12 and 24 months including hospital admission days, blood product usage and days on intravenous antibiotics and antifungals; health-related quality of life at month 3, 6, 12, 18 and 24; change in performance status from baseline at month 3, 6, 12, 18 and 24, and; change in Comprehensive Geriatric Assessment (CGA) [30] from baseline at month 12 and 24.

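### Adverse event reporting ends 28 days after the last dose, so the 12- and 24-month grade 3–4 adverse event outcome compares the arms over unequal observation periods

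*Protocol article*

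**What the plan says.** Under Trial outcomes, the article names as a secondary outcome the "cumulative occurrence of grade 3 and 4 adverse events at 12 and 24 months". Under Adverse events reporting and analysis, the reporting period starts with protocol treatment and runs "for up to 28 days after the last dose of investigational medicinal product (IMP". No section shown extends it, although under Study design patients enter a trial "with participants followed up for at least two years".

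The arms differ in planned treatment length. Under Interventions, "cycles are up to 42 days in duration; this includes a 28-day treatment cycle" in both arms. The rule for starting further cycles covers "cycle 2–4 of DAGO and cycle 2–12 of VEN + LDAC", and Table 2 notes for VEN + LDAC that "up to 12 cycles may be given". Some DAGO patients may also be allowed "to crossover to receive VEN + LDAC treatment for up to 12 cycles".

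Under Statistical analysis plan, binary outcomes that record whether an event occurred are analysed with a beta-binomial model and a difference in proportions. The AE outcome is not labelled treatment-emergent, and no exposure adjustment is mentioned.

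**The concern.** A cumulative proportion at a fixed time compares two arms fairly only if both are observed to that time, or if the analysis allows for the shortfall. Here observation is tied to the last dose, and the last dose comes at very different times by design. An event in month 8 is reported for a patient still on VEN + LDAC and not reported for a patient who finished DAGO in month 4.

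This matters because lower toxicity is part of the rationale. The Abstract presents VEN + LDAC as less toxic, Sample size determination accepts a loss in mEFS because of the regimen's other benefits, and Statistical analysis plan aims to show greater benefit on secondary outcomes. The Background also cites serious long-term effects of intensive chemotherapy. Later effects of that kind, and toxicity of salvage or transplant, fall outside the DAGO window.

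The problem cannot simply be left to a later analysis plan. Analysis can adjust for exposure, but it cannot recover events that sites were not asked to report.

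**Working it through.** The article gives no length of AE surveillance, so there is no stated figure to reproduce. The windows follow from its schedule.

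**Inputs**
- Cycle length c: 28 days at the shortest, up to 42 (Interventions).
- DAGO: four cycles. The last dose is on day 5 of cycle 4 in every age band (Table 2).
- VEN + LDAC: up to twelve cycles, with venetoclax to day 28 of each (Table 2).
- Reporting tail: 28 days.
- Pace check: Tissue and blood samples places a marrow sample "at month six (which will usually be the post-cycle 4 time point", which implies c = 182.6/4 = 45.7 days.
- One month = 30.44 days.
- Assumptions: the DAGO drugs count as IMPs for the 28-day rule, and time runs from the start of treatment.

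**Formulas**
- DAGO, full course: 3c + 5 + 28
- VEN + LDAC, twelve cycles: 11c + 28 + 28
- VEN + LDAC, four cycles: 3c + 28 + 28

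**Results: day on which AE reporting closes**

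| Cycle length | DAGO, 4 cycles | VEN + LDAC, 12 cycles | VEN + LDAC, 4 cycles |
|---|---|---|---|
| 28 days | 117 (3.8 months) | 364 (12.0 months) | 140 (4.6 months) |
| 42 days | 159 (5.2 months) | 518 (17.0 months) | 182 (6.0 months) |
| 45.7 days | 170 (5.6 months) | 558 (18.3 months) | 193 (6.3 months) |

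**Share of the outcome period covered**
- To month 12: DAGO 117/365.25 = 32% to 159/365.25 = 44% (47% at the month-six pace). Twelve cycles of VEN + LDAC: about 100%.
- To month 24: DAGO 16% to 22% (23%). Twelve cycles of VEN + LDAC: 50% to 71% (76%).

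**Early stopping.** A DAGO patient who stops after cycle 2 has a last dose on day 8 of that cycle. The window closes at c + 8 + 28, which is day 64 to 78.

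**Crossover.** If reporting continues after crossover, a patient who moves directly to twelve VEN + LDAC cycles after two DAGO cycles has a window of 2c + 11c + 56. That is 420 to 602 days, or 13.8 to 19.8 months. Capture within the DAGO arm would then range from about 2 months to nearly 20, and the longer windows include AEs of the other regimen.

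**The case against.** The strongest reply is that the two passages can be read together. The reporting period defines which AEs count, and the outcome is a treatment-emergent count at two cut-offs. Toxicity over the whole of each regimen is a legitimate measure of burden, and a regimen with more cycles has more time to cause it. This stands in part: such a count can be tabulated, and for a VEN + LDAC patient who takes all twelve cycles the 12-month figure is essentially complete. A reader might infer that the outcome cannot be measured at all, and the document does not support that. But the outcome is not labelled treatment-emergent, and the 24-month DAGO figure without crossover adds nothing after about month 4 to 6.

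A reader might also infer a size. If the event rate were equal and constant in both arms on and off treatment, a twelve-cycle VEN + LDAC patient would show 365/159 = 2.3 to 365/117 = 3.1 times as many events by month 12. The document does not support that assumption. The Background attributes the toxicity of intensive chemotherapy mainly to prolonged myelosuppression, which would fall mostly around the cycles and so inside the window. No AE rate is given.

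Four further points limit the concern:
- Twelve cycles is a maximum, and the share of patients expected to reach it is not given.
- Crossover may reopen reporting for some DAGO patients, in some cases perhaps past month 24.
- Overall survival, resource use, quality of life, performance status and geriatric assessment are collected to month 24 and capture some of the late burden.
- The main distortion runs against VEN + LDAC, so it is not a route to a spurious toxicity benefit.

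**Conclusion.** The concern holds as a mismatch between one secondary outcome and the period over which its data are collected. For full courses without crossover, AE capture ends at about 4 to 5.6 months on DAGO and about 12 to 17 months on VEN + LDAC (4.6 to 6.0 months if only four cycles are given). On the 28- to 42-day schedule neither arm is covered to month 24. The beta-binomial difference in proportions makes no allowance for this.

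The likely direction is over-counting of VEN + LDAC relative to DAGO, together with missed late and post-salvage or post-transplant toxicity after DAGO. A real toxicity advantage could be hidden or reduced. It would go too far to say that the toxicity conclusion will be wrong. The direction is a tendency, because early stopping of VEN + LDAC narrows the gap and crossover lengthens capture for some DAGO patients. The size depends on when AEs occur and how many cycles are given, and the document states neither.

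The mEFS analysis, the margin, the sample size and the go decision are not affected. This should be fixed, but it does not threaten the trial's main conclusion.

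**What to change.** Reconcile Trial outcomes with Adverse events reporting and analysis in one of two ways.

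1. **Extend collection.** Record grade 3 and above AEs in both arms over the same period from randomisation, regardless of treatment status, to month 12, and to month 24 if that time point is kept. Use existing follow-up contacts. Sampling is three-monthly to two years, but with an exception for confirmed molecular persistence, so those patients need another contact, such as the quality-of-life time points. The full schedule of events is in a supplement not shown here and should be checked.
2. **Restate the outcome.** Define it as treatment-emergent AEs over a common window covered in both arms, and add rates per patient-month of AE surveillance. Patients who stop early must still be followed to the end of that window. On the shortest schedule a full DAGO course is covered only to day 117.

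Under either option, state whether reporting continues after crossover, and present AEs before and after crossover separately.

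The cost is modest: revised AE wording and some extra eCRF entry during follow-up under the first option, or loss of the 24-month AE outcome under the second. Recruitment opened in June 2021, so events already past the window in early patients may be hard to recover. That favours deciding soon.

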### Dose modifications and discontinuations

Recommended dose modifications are listed in Table 3.

**Table 3 Tab3:** Recommended dose modifications within the VICTOR trial

Standard of Care (DAGO) Arm	
**Observation**	**Recommended Modification**
Serum creatinine (mmol/L)	Daunorubicin dose
< 105	100%
105–265	75%
> 265	50%
Bilirubin > 2 × ULN and AST/ALT > 2.5 × ULN	Postpone gemtuzumab ozogamicin dose until less than these levels. Consider omitting the scheduled dose if delayed more than 2 days between sequential infusions
Bilirubin (μmol/L)	Daunorubicin dose
< 20	100%
20–50	75%
> 50	50%
Bilirubin (μmol/L)	Cytarabine dose
> 34	50%

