**Venetoclax and Low-dose Cytarabine Arm**	
During venetoclax maintenance:	
Upon reoccurrence of grade 3 or 4 non-haematological toxicity, or grade 4 haematological toxicities, except lymphopenia	
**Dose at interruption (mg)**	**Restart dose (mg*)**
400	300
300	200
200	100
100	50**

^*^ The modified dose should be continued for 1 week before increasing the dose

^**^ As the venetoclax is only available in 100 mg strength, if a dose reduction to 50 mg is required, the patient should take 100 mg every other day

*ALT* alanine aminotransferase, *AST* aspartate transaminase, *ULN* upper limit of normal

If signs and symptoms of veno-occlusive disease or sinusoidal obstruction syndrome occur in patients treated with gemtuzumab ozogamicin (GO), defibrotide treatment can be considered and GO should be discontinued.

For patients receiving VEN and experiencing grade 3–4 abnormal liver function tests VEN and any potentially hepatotoxic drugs (including azole antifungals) should be withheld until these have resolved to grade 2 or below. Venetoclax (and the azole antifungal if applicable) should be restarted at the original dose. During maintenance, venetoclax may be withheld for any grade 3 or 4 non-haematological toxicity, or grade 4 haematological toxicities (except lymphopenia). Once the toxicity has resolved to grade 1 or baseline level (recovery), therapy with VEN may be restarted at the same dose. If the toxicity recurs, and for any subsequent occurrences, the dose reduction guidelines in Table 3. For patients who require dose reductions to less than 100 mg for more than 2 weeks, discontinuation of VEN should be considered.

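### Isolated grade 3–4 AST/ALT rises, and liver events between DAGO doses, are reported almost automatically on venetoclax but on DAGO only through another intervention or investigator judgement

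*Protocol article*

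**What the plan says.** In the protocol article, Adverse events reporting and analysis asks for all adverse events of grade 3 and above, "with the exception of abnormal laboratory findings which should only be reported if the event" meets one of two conditions. The first is early discontinuation of trial treatment. The second reads: "Requires a dose modification or interruption or any other therapeutic intervention or is judged to be of significant clinical importance". The same filter applies to both arms.

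The action rules that feed this filter are in Dose modifications and discontinuations, and they differ by arm.

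- **VEN + LDAC.** The text below Table 3 says: "For patients receiving VEN and experiencing grade 3–4 abnormal liver function tests VEN and any potentially hepatotoxic drugs (including azole antifungals) should be withheld".
- **DAGO.** Table 3 adjusts daunorubicin on serum creatinine and bilirubin, and cytarabine on bilirubin. AST/ALT appears only in the gemtuzumab ozogamicin (GO) row, whose condition is "Bilirubin > 2 × ULN and AST/ALT > 2.5 × ULN" and whose action is "Postpone gemtuzumab ozogamicin dose until less than these levels", with omission to be considered after a longer delay.

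Trial outcomes lists as a secondary outcome the "cumulative occurrence of grade 3 and 4 adverse events at 12 and 24 months". The Statistical analysis plan section makes it part of the aim to show greater benefit of VEN + LDAC on secondary outcomes. Study design describes the trial as non-blinded.

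**The concern.** Whether a grade 3–4 laboratory abnormality enters the adverse event data depends largely on whether the treatment rules call for action, and those rules are not the same in the two arms. For one kind of event, an isolated transaminase rise, the venetoclax arm has a written instruction that satisfies the reporting condition and the DAGO arm has none. Timing adds to this. Venetoclax is taken throughout the 28-day treatment cycle, while DAGO drugs are given in a short block at its start, so a DAGO liver abnormality that comes and goes between doses has no dose to modify.

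At stake is the between-arm comparison of grade 3–4 adverse events. Equal true liver toxicity could be reported unequally, making VEN + LDAC look relatively more hepatotoxic and understating toxicity on DAGO. Because the trial is open-label, the judgement that fills the gap on DAGO is made by someone who knows the treatment. An event never entered cannot be recovered by any later analysis of the reported events.

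**Working it through.** The plan states no figure on this point, so there is none to reproduce. The check sets the reporting filter against the action rules, then counts dosing days.

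**1. Filter against action rules** (Adverse events reporting and analysis; Table 3 and the text below it)

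| Grade 3–4 finding | While taking venetoclax | On DAGO |
|---|---|---|
| Isolated AST/ALT rise | Withhold: interruption condition met | No rule for daunorubicin or cytarabine; GO rule not met without bilirubin. Reported only through another intervention or judged importance |
| AST/ALT and bilirubin both raised | Withhold: condition met | GO postponed if a GO dose is due; bilirubin rules apply if daunorubicin or cytarabine is due |
| Bilirubin at a dosing time | Withhold: condition met | Dose reduction: condition met (step 3) |
| Any liver test between doses, resolved before the next dose | Withhold if within days 1–28: condition met | No dose to modify. Reported only through another intervention or judged importance |

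**2. Days on which a trial drug is scheduled** (Interventions, Table 2)

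- VEN + LDAC, cycles 1–4: 4 × 28 = 112 days.
- DAGO, age 60–69: 10 + 8 + 3 + 3 = 24 days (cytarabine on days 1, 3 and 5 in cycles 3 and 4).
- DAGO, age 70 and over: 10 + 8 + 5 + 5 = 28 days.
- Share of four 28-day treatment cycles (112 days): VEN + LDAC 112/112 = 100%; DAGO 24/112 = 21% to 28/112 = 25%.
- Share of four maximum-length 42-day cycles (168 days): VEN + LDAC 112/168 = 67%; DAGO 24/168 = 14% to 28/168 = 17%.
- The one DAGO rule that uses AST/ALT concerns two GO days in cycle 1: 2/112 = 1.8%. Where GO is not yet available (New Zealand, footnote to Table 2) it covers no days.
- Venetoclax may continue to 12 cycles: 12 × 28 = 336 days.

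These counts show when a dose could be modified. They are not rates of reporting.

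**3. Bilirubin on DAGO**

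The article gives neither the grade 3 cut-off nor the upper limit of normal (ULN). Assume that grade 3 begins above 3 × ULN and that ULN lies between 17 and 22 μmol/L. The grade 3 threshold is then 3 × 17 = 51 to 3 × 22 = 66 μmol/L. Table 3 takes daunorubicin to 50% above 50 μmol/L and cytarabine to 50% above 34 μmol/L. Both cut-offs lie below 51 to 66 across the whole assumed range. A grade 3 bilirubin when one of these drugs is due therefore calls for a dose change and is reportable on DAGO as well.

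**4. Form of the bias**

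Let p be the true proportion with an isolated grade 3–4 AST/ALT rise, equal in both arms, and c the proportion of these reported on DAGO, with near-complete reporting on venetoclax. The spurious difference is p × (1 − c). Neither p nor c is in the documents. Purely as an assumption, p = 10% with c from 25% to 100% gives 10 × 0.75 = 7.5 percentage points down to 0. The gap comes entirely from the assumed c.

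**The case against.** The filter is not purely action-driven. Its clinical-importance limb needs no action, and its reference to any other therapeutic intervention is not tied to a trial dose. Both apply equally to the two arms. A reader might infer that the same liver event is always an adverse event on VEN + LDAC and usually not one on DAGO. The documents do not support that.

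- "Always" fails because the withholding rule covers patients receiving venetoclax. It does not reach the day 29–42 recovery window or the time after venetoclax stops.
- "Usually not" fails because DAGO has its own bilirubin, creatinine and GO rules, and nothing in the article gives a frequency. Table 3 is headed as recommended modifications and DAGO may follow local practice, so a missing AST/ALT row does not prove that no action would follow.

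A reader might also take 112/28 = 4 as four times the chance of being reported. That would need abnormalities spread evenly over time and resolving at once. An abnormality that persists to the next DAGO dose can still trigger a modification where a rule exists.

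The consequence is limited too. The go decision rests on molecular event-free survival alone, and the bias runs against the experimental arm. The schedule of events, the adverse event definitions and the case report form are in material not shown, so laboratory values may already be collected separately.

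All of this stands and confines the point to isolated transaminase rises and to liver events outside DAGO dosing days. It does not remove the point. For those events the reporting rule, as printed, is met by instruction in one arm and by discretion or an unrelated intervention in the other.

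**Conclusion.** The point holds in a limited form. For isolated grade 3–4 AST/ALT rises, and for liver events outside DAGO dosing days, ascertainment is near-automatic while venetoclax is being taken. On DAGO it depends on another intervention or on unblinded judgement. The likely direction is more reported liver toxicity on VEN + LDAC. The size cannot be derived from the documents: the dosing-day counts (112 against 24 to 28) describe opportunity only, and any percentage gap rests on an assumed DAGO capture rate.

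For grade 3–4 bilirubin at a DAGO dosing time there is probably no asymmetry, given the assumed grade 3 cut-off and ULN range. The primary outcome and the non-inferiority decision are not affected. The weakness is in one laboratory component of a secondary safety outcome, and it can be corrected only at the point of data collection.

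**What to change.** Amend Adverse events reporting and analysis so that every grade 3–4 ALT, AST, bilirubin and creatinine value obtained in the adverse event reporting period is recorded in both arms by CTCAE grade, whatever action followed. Creatinine belongs on the list because its action rule also differs by arm: Table 3 ties it to daunorubicin only.

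Compare the arms on these four tests from the recorded values and not from the reported adverse events. Use a common window, such as the first four cycles, because venetoclax may run to 12 cycles against four on DAGO and reporting continues to 28 days after the last dose.

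Keep the stated cumulative grade 3–4 outcome as it is, with its other laboratory events. Taking those out would redefine a stated outcome after recruitment opened and could remove cytopenias. No dose rule needs to change.

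The cost is a wording change, a short case report form addition and modest extra entry of results already in the notes, including back-entry for patients already enrolled. If the values are already captured, only the wording and the planned comparison change. One limit remains: a comparison of values still depends on how often each arm is tested, so the number of tests per patient should be shown beside it.
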